#### 2.11.2. Secondary outcome measurement.

##### 2.11.2.1. Laboratory indicators.

In this study, all subjects will be measured for ESR, CRP, RF, IL-1β, IL-6, TNF-α, IL-18, MMP-3 in serum. ESR, CRP, and RF will be detected by automatic biochemical analyzer, while IL-1β, IL-6, TNF-α, IL-18, and MMP-3 via ELISA. Group D will be tested only one time during the study while RA patients will be tested before the treatment and 6 weeks after the treatment by a way that four equidistant time points within 24 hours for blood sampling. Except for this, RA patients will be examined after a 3 -week and 3- month intervention.

##### 2.11.2.2. Joints morning stiffness score.

It refers to the time required for the patient to start activities after waking up to the obvious relief of morning stiffness symptoms, calculated in minutes. Score calculation method: no morning stiffness, 0 point; morning stiffness time <1 hour, 2 points; 1 hour ≤morning stiffness time <2 hours, 4 points; Morning stiffness time >2 hours, 6 points. The higher the score, the more serious of the disease.

##### 2.11.2.3. Joints swelling index.

Joints swelling index is evaluated by observing 28 joints of the whole body to judge the degree of swelling. Grade the swelling of the joints: no swelling, 0 point; swelling lower than the nearby bone markers, 1 points; swelling as tall as the bone markers, 2 points; swelling higher than the nearby bone markers, 3 points. The joint swelling index, expressed as a sum, where each joint is graded for swelling on a scale of 0 none, 1 mild, 2 moderate, and 3 severe. The higher the score, the more serious the condition.

##### 2.11.2.4. Joints tenderness index.

Joints tenderness index is to judge whether there is tenderness and record the number of tenderness of 28 joints. It is graded as follows: no tenderness, 0 point; tenderness with flinch, 2 points; tenderness with flinch and avoidance, 3 points. The higher score, the more severe pain and dysfunction.

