##### 2.11.2.5. Disease activity score of 28 joints (DAS28).^[16]^

DAS 28 is one of the most commonly and widely method to evaluate RA disease activity in clinic. It is comprised of tenderness and swelling of 28 joints such as shoulder, elbow, knee, wrist, MCPs, and PIPs. It is calculated by swollen joint count (SJC), tender joint count (TJC), a marker of inflammation like CRP or ESR, visual analog scale (VAS), general health (GH). DAS28 scores were categorized as low (<3.2), moderate (<5.1), or high (≥5.1). The higher the score, the higher the activity of the RA disease.

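### The joint tenderness index has no score for a joint that is tender without flinch, and does not say how the 28 joints combine into one value

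*Protocol article*

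**What the plan says.** The joint tenderness index is one of five secondary outcomes in section 2.11.2 of the protocol article. Table 1 schedules it at baseline, week 3, week 6 and month 3. Section 2.11.2.4 first describes the task: "judge whether there is tenderness and record the number of tenderness of 28 joints". It then gives the grading: "no tenderness, 0 point; tenderness with flinch, 2 points; tenderness with flinch and avoidance, 3 points". It closes with the direction of the scale only: "The higher score, the more severe pain and dysfunction".

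The neighbouring swelling index in 2.11.2.3 is fully specified. It has a lowest positive level, "swelling lower than the nearby bone markers, 1 points", and an aggregation rule: "The joint swelling index, expressed as a sum, where each joint is graded for swelling on a scale of 0 none". Section 2.11.2.5 separately lists a tender joint count among the components of DAS28 and does not relate it to the tenderness index.

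**The concern.** Two things are incomplete in the scoring rule as written.

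- **A state without a score.** Tenderness without flinch is the mildest positive finding. It is not absence of tenderness, and it does not meet the definition of the 2-point level. An assessor who follows the text has no permitted entry for it.
- **No rule for the total.** The section uses the language of a count and then the language of a grade, and never says how the joints are combined.

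The first gap affects the score of the single joint; the second affects only the patient's total. What is at stake is the precision of a secondary efficacy outcome and the meaning of its reported value. Change is touched directly, because a joint that improves from flinching to mere tenderness moves into the undefined state.

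**Working it through.** The plan states no figure that depends on this index, so there is nothing to reproduce. The check sets the two joint indices side by side and then does simple arithmetic.

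| Feature | Swelling (2.11.2.3) | Tenderness (2.11.2.4) |
|---|---|---|
| Levels | 0, 1, 2, 3 | 0, 2, 3 |
| Mildest positive finding | defined, 1 point | not defined |
| Aggregation | sum over joints | not stated |

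**Possible range.** With 28 joints and a maximum of 3 points per joint, a count runs from 0 to 28 and a graded sum from 0 to 28 × 3 = 84.

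**One joint, one visit.** A joint tender without flinch may be entered as 0, as 2, as 1 by an unwritten convention, or left blank. The spread between the numerical entries is 2 − 0 = 2 points.

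**One joint, change between visits.** Suppose a joint is tender with flinch at baseline (2 points) and tender without flinch at week 6. The recorded improvement is 2 − 2 = 0, 2 − 1 = 1 or 2 − 0 = 2 points, depending on the convention.

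**One patient (assumed joints, not from the documents).** Take 10 tender joints: 6 without flinch, 3 with flinch, 1 with flinch and avoidance.

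- Count: 10.
- Graded sum, undefined joints scored 0: 6 × 0 + 3 × 2 + 1 × 3 = 9.
- Graded sum, undefined joints scored 1: 6 × 1 + 3 × 2 + 1 × 3 = 15.
- Graded sum, undefined joints scored 2: 6 × 2 + 3 × 2 + 1 × 3 = 21.

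The same examination gives 9, 10, 15 or 21.

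**Dependence on the assumption.** With k such joints, the spread of the graded sum is 2k: 4 points for k = 2, 8 for k = 4, 16 for k = 8. The documents give no value for k, and no standard deviation or expected difference for this index. The spread therefore cannot be turned into a loss of power.

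**What the gap does not reach.** The primary outcome is SF-MPQ (2.11.1). The sample size in 2.12 uses DAS28. The DAS28 component is a count of tender joints, which needs no grade.

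**The case against.** The strongest reply is that this is a line lost in condensing the protocol, with little consequence. The jump from 0 to 2 looks like a dropped level. Section 2.15 promises a standardized case report form with detailed recording rules, and staff training that covers effect assessment; either could impose one convention. This stands in part: it is why the text supports only that joints *can* be scored differently. It does not remove the point. The article chose to print the scoring rule, the rule is incomplete, and nothing else in the document completes it.

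A second reply is that skipping a number is not itself an error, since the morning stiffness score in 2.11.2.2 uses 0, 2, 4 and 6. That is right, but the defect here is a clinical state with no score, not the absence of the digit 1.

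A third reply is that the text leans towards a graded index: it speaks of grading and of a higher score, it follows a graded and summed swelling index, and DAS28 already supplies a count. This has force. The missing aggregation rule is the weaker half of the point, although the count wording remains and no sum is stated.

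A reader might go further and infer any of the following. The documents support none of them.

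- That assessors will disagree, or that error between hospitals will result. The trial has four hospitals, but the number of assessors and their assignment are not described.
- That the patients most likely to improve are the ones misclassified. Nothing says who is likeliest to improve.
- That one arm is favoured. Assessors are to be blinded (2.2 and 2.5), and if that holds, inconsistent scoring should mainly add noise.

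**Conclusion.** The point holds as a defect in the definition of a secondary outcome. Section 2.11.2.4 leaves tenderness without flinch unscorable and states no aggregation rule. The size is up to 2 points per affected joint in a graded sum, and a possible range of 0 to 28 or 0 to 84 depending on the reading. Any figure per patient rests on an assumed number of such joints.

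The expected consequence is added measurement error in this index. The correction should be made, but the finding does not threaten the trial's main conclusion: the primary outcome, the sample size and the DAS28 tender joint count are untouched.

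**What to change.** Check section 2.11.2.4 against the source scale and the case report form. Then:

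- add the missing level, tenderness without flinch, 1 point, so that the grades run 0-1-2-3 as for swelling;
- state that the index is the sum of the grades over the 28 joints, range 0 to 84;
- state that it is distinct from the tender joint count (0 to 28) that DAS28 already requires, so that the count wording no longer defines the index.

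The cost is about one line in 2.11.2.4 and the matching line on the case report form. It should be done before data are scored, because a grade that was not recorded at the visit cannot be recovered afterwards.

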##### 2.11.2.5. Disease activity score of 28 joints (DAS28).^[16]^

DAS 28 is one of the most commonly and widely method to evaluate RA disease activity in clinic. It is comprised of tenderness and swelling of 28 joints such as shoulder, elbow, knee, wrist, MCPs, and PIPs. It is calculated by swollen joint count (SJC), tender joint count (TJC), a marker of inflammation like CRP or ESR, visual analog scale (VAS), general health (GH). DAS28 scores were categorized as low (<3.2), moderate (<5.1), or high (≥5.1). The higher the score, the higher the activity of the RA disease.

### 2.12. Sample size calculation

The sample size has been estimated based on the results of a preceding study that had shown that moxibustion can ease RA patients.^[10]^ Results from a previous study showed that the mean changes in the Disease activity score in 28 joints (DAS 28) were 4.17 ± 0.94 (moxibustion group) and 4.86 ± 1.40 (control group). PASS software was used to calculate the sample size. The confidence of the trial sample size was 90% and the significance level was 0.05. Results showed that clinically significant differences would be detected using a minimum sample size of 26 individuals in each group. The maximum permissible withdrawal rate is 15% and 120 participants (30 per group) will be recruited.

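### The DAS28 planning figures are labelled as mean changes, which does not fit a benefit of moxibustion; the label should be checked and corrected, and the 90% power restated

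*Protocol article*

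**What the plan says.** Section 2.12 (Sample size calculation) bases the trial's size on "a preceding study that had shown that moxibustion can ease RA patients", with a citation. The next sentence, which carries no citation of its own, gives the planning figures from a previous study: "mean changes in the Disease activity score in 28 joints (DAS 28) were 4.17 ± 0.94 (moxibustion group) and 4.86 ± 1.40 (control group"). It continues: "The confidence of the trial sample size was 90% and the significance level was 0.05". The result is "a minimum sample size of 26 individuals in each group", and then: "The maximum permissible withdrawal rate is 15% and 120 participants (30 per group) will be recruited".

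Section 2.11.2.5 sets the direction of the scale: "The higher the score, the higher the activity of the RA disease". It also gives bands: "DAS28 scores were categorized as low (<3.2), moderate (<5.1), or high (≥5.1").

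Section 2.13 (Statistical analysis) names one-way ANOVA with multiple comparisons, Student t tests for pairs of groups, and Tamhane T2 where the assumptions fail. It does not say whether these act on levels or on changes from baseline, and it names no baseline-adjusted model.

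**The concern.** A mean change in a score where higher is worse can be reported as a fall or as a signed difference. Under the first convention the control group improved more than the moxibustion group. Under the second both groups deteriorated by a large amount, moxibustion somewhat less. A study summarised as "had shown that moxibustion can ease RA patients" should show neither pattern.

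These four numbers are the only quantitative basis given for the trial's size. If the label is wrong, a reader cannot tell which quantity the calculation was meant to compare, whether the SDs belong to levels or to changes, or from the figures alone that the planned effect favours moxibustion. Because the analysis section does not name the quantity either, the label in section 2.12 is the only clue.

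**Working it through.** **Step 1: test the label against the scale.** The inputs are 4.17 (moxibustion) and 4.86 (control) from section 2.12, and the scale direction from section 2.11.2.5.

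| Reading | Meaning | Fits a benefit of moxibustion? |
|---|---|---|
| Falls from baseline | Control improved more, by 4.86 − 4.17 = 0.69 | No |
| Signed rises from baseline | Both groups worsened, by 4.17 and 4.86 | Poorly: moxibustion worsened by 0.69 less, but by more than 4 points |
| Post-treatment levels | Both lie between 3.2 and 5.1 (moderate band); moxibustion lower by 0.69 | Yes |

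Size points weakly the same way. A mean fall of 4.86 that ended at the 3.2 bound would start from 4.86 + 3.2 = 8.06, well above the 5.1 threshold for high activity. The protocol does not rule out such a baseline, so this supports the argument but does not carry it. No other section corrects the label.

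**Step 2: try to reproduce the stated 26 per group.** Inputs:

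- difference δ = 0.69;
- SDs 0.94 and 1.40, so the pooled SD = √((0.94² + 1.40²)/2) = √1.4218 = 1.192, and δ/SD = 0.579;
- significance level 0.05, taken as two-sided because the protocol does not say;
- the 90% that the protocol calls confidence, read as power.

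Normal approximation: n = 2 × SD² × (1.960 + 1.282)² / δ² = 2 × 1.4218 × 10.507 / 0.4761 = 62.8, so 63 per group. The noncentral t gives 64. The stated 26 is not reproduced. A one-sided test at 90% would still need 52, and a two-sided test at 80% would need 48 (noncentral t).

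**Step 3: does correcting the label change this?** The formula uses only |δ| and the SDs. If the trial compares the same quantity that the figures describe, whether change with change or level with level, the inputs are the same and the answer is 64 both times.

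**Step 4: power at the planned sizes.** Noncentrality = δ / (SD × √(2/n)), two-sided 0.05.

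| n per group | Noncentrality | Power |
|---|---|---|
| 26 | 2.09 | 53% |
| 30 | 2.24 | 60% |
| 64 | 3.27 | 90% |

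**Step 5: where the type of SD would matter.** It matters only if the figures are levels and the trial analyses something else. For a baseline-adjusted comparison the SD becomes 1.192 × √(1 − r²), where r is the correlation of baseline with outcome. The protocol gives no r, so the values below are assumptions.

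| Assumed r | Adjusted SD | Power at 26 per group |
|---|---|---|
| 0.3 | 1.137 | 57% |
| 0.5 | 1.033 | 66% |
| 0.7 | 0.852 | 82% |
| 0.8 | 0.715 | 93% |

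**The case against.** The strongest reply is that this is a slip of one word. A two-sided calculation ignores the sign of the difference, so the required number is the same under either label. That stands. A reader might infer that the mislabel is what makes the stated 26 wrong; the documents do not support that, because 26 does not follow from the inputs under either label.

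A reader might also infer that the same inputs imply widely different sample sizes depending on what they are. Such a range needs correlations that the protocol does not give and analyses (change scores, baseline adjustment) that section 2.13 does not name. It reflects the values assumed and is not a property of the planning figures.

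It is also fair to say that the claim of benefit and the figures stand in adjacent sentences, and only the first carries a citation. The contradiction therefore assumes that both refer to one study. This is the natural reading, but the text does not state it. Likewise, a reader might conclude that the figures must be end-of-treatment levels. They fit best as such, but only the cited study can settle it, and whether the 0.69 includes a baseline imbalance in that study cannot be checked here.

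What remains is a label that does not fit the direction of the scale and the stated benefit, attached to a power that the printed figures do not give.

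**Conclusion.** The label is wrong as written, provided the two adjacent sentences describe one study. As mean changes, the figures either favour control by 0.69 or show both groups worsening by more than 4 points. Post-treatment levels are the probable meaning, subject to the source.

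Correcting the label leaves the required size at 64 per group for a like-with-like comparison. The restated power is about 53% at the minimum of 26 and about 60% at 30 if nobody withdraws, against the 90% claimed. These figures rest on a two-sided 0.05 test, a pooled SD of 1.192, a single pairwise comparison without adjustment for multiple comparisons, and the 90% being meant as power. The point should be corrected, but it does not show that the trial was planned on an effect in the wrong direction.

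**What to change.** 1. Check the cited study and replace the label in section 2.12 with what the figures are. If they are post-treatment levels, say so and give the time point.
2. State the planned effect with its direction, for example a difference of 0.69 in post-treatment DAS28 in favour of moxibustion if the source confirms that reading, and say that both sentences refer to the same study if they do.
3. Replace the 90% with the power of the unadjusted comparison that section 2.13 names: about 53% at 26 and 60% at 30 per group. Say whether the test is two-sided.
4. Optional, and only if a baseline-adjusted analysis is adopted: show power at 26 per group for the range of correlations in the working, marked as assumptions.

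The cost is a look at the source, a few corrected sentences and a rerun of the calculation. No patients are added. The price is a less favourable stated power.

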## 2. Methods

### 2.1. Study design

The study aims to assess the effectiveness of moxibustion for RA, as well as to determine which time is more optimal in clinical practice. In addition, it will explore the influence of Chrono-moxibustion on circadian rhythm of RA patients. According to the validity of Chrono-moxibustion may adjust circadian rhythm of RA patients, we hypothesized there will be diverse effect by Chrono-moxibustion based on the theory of Chronobiology, moreover, it can also modulate the pathological rhythm of RA.

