### 2.4. Randomization and allocation concealment

Eligible patients will be randomly assigned to 3 groups in a 1:1:1 ratio. The computer-generated random number list will be concealed in sequentially numbered, opaque, and sealed envelopes which kept by an independent custodian to ensure allocation concealment. The patients’ screening sequence numbers will be printed on the outside while the group names will be printed inside the envelope. The practitioner will firstly verify each patient meet the eligibility criteria and sign the written informed consent form, and then open the sealed envelope which containing an allocation sequence number for each patient. If any error or disclosure regarding randomization occurs, a new randomization sequence will be generated starting from the problematic serial number and applied to subsequent patients from then on.

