In summary, the results of this research will be expected to confirm whether Chrono-moxibustion can alleviate RA, and point out which time the effect will be better, so as to help doctors and patients to select an optimal treatment time. Combined with the laboratory indicators results, it will help us to reveal the mechanism of Moxibustion in the treatment of RA. We believe that the results will engender a positive impact on moxibustion in the treatment of RA.

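### The sample size rests on moxibustion versus control and contains no 7–9 am versus 5–7 pm difference, yet the plan promises to name the better treatment hour

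*Protocol article*

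**What the plan says.** All references are to the Protocol article.

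- **Section 2.12 (sample size).** The calculation is "based on the results of a preceding study that had shown that moxibustion can ease RA patients". Its only figures are DAS28 values of "4.17 ± 0.94 (moxibustion group) and 4.86 ± 1.40 (control group". It continues: "The confidence of the trial sample size was 90% and the significance level was 0.05". It concludes that "clinically significant differences would be detected using a minimum sample size of 26 individuals in each group", and then that "The maximum permissible withdrawal rate is 15% and 120 participants (30 per group) will be recruited".
- **Section 2.4.** "Eligible patients will be randomly assigned to 3 groups in a 1:1:1 ratio": A (7–9 am), B (5–7 pm) and C (waiting list). Group D is healthy controls.
- **Section 2.1.** The aims are to assess the effectiveness of moxibustion, "as well as to determine which time is more optimal in clinical practice".
- **Section 3, closing paragraph.** The results are expected to "point out which time the effect will be better, so as to help doctors and patients to select an optimal treatment time".
- **Section 2.13.** Group comparisons use one-way ANOVA with multiple comparisons and pairwise t tests.
- **Section 2.11.** SF-MPQ is the primary outcome; DAS28 is secondary.
- **Section 1.** A pilot study is said to suggest different effects at different times, but no figure from it is given.

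**The concern.** Choosing between two hours means comparing A with B, two arms that receive the same Du moxibustion at different times of day. The contrast in 2.12 is moxibustion against no moxibustion, which corresponds to A or B against C. The first effect says nothing about the size of the second, so a calculation for one does not size the other. The sentence on clinically significant differences names no contrast, so it can be taken to cover the timing aim as well.

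The stake is the conclusion on timing. A non-significant A–B test could be read as showing that the hour does not matter. Equally, if one arm reaches P < .05 against the waiting list and the other just misses, the first hour could be called optimal although the two hours were never shown to differ.

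**Working it through.** **Inputs.** From 2.12: means 4.17 and 4.86, SDs 0.94 (moxibustion) and 1.40 (control), alpha 0.05, 26 per group needed and 30 recruited. The stated 90% confidence is read as power. Sidedness is not stated; two-sided is used unless noted. The difference is 4.86 − 4.17 = 0.69. The A–B difference is not in the document, so the full 0.69 and half of it (0.345) are assumptions that span a range.

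**Formulas.** Standard error SE = SD × √(2/n). Power comes from the noncentral t distribution with 2n − 2 degrees of freedom and noncentrality (difference)/SE. The 95% CI half-width is t(0.975; 2n − 2) × SE.

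**1. The plan's own figure, moxibustion versus control.** Root-mean-square SD = √((0.94² + 1.40²)/2) = 1.19; standardised difference 0.69/1.19 = 0.58.
- 90% power needs 64 per group by t (63 by the normal approximation), or 52 one-sided.
- At 26 per group: SE = 1.19 × √(2/26) = 0.331, noncentrality 2.09, power 53% (55% by the normal approximation).
- At 30 per group: SE = 0.308, noncentrality 2.24, power 60%.

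So 26 does not reproduce for the contrast it was calculated for. This matters for the fix.

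**2. A versus B.** Both arms receive moxibustion, so 0.94 is the plan's natural SD; 1.40 is shown as an outer bound.

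| A–B difference | SD | Power, 26/group | Power, 30/group |
|---|---|---|---|
| 0.69 (all of it) | 0.94 | 74% | 80% |
| 0.345 (half) | 0.94 | 26% | 29% |
| 0.69 | 1.40 | 41% | 47% |
| 0.345 | 1.40 | 14% | 16% |

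For the first row: SE = 0.94 × √(2/26) = 0.261, noncentrality 0.69/0.261 = 2.65; at 30 per group SE = 0.243, noncentrality 2.84.

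**3. What 30 per group can show for A versus B.**
- Difference detectable with 90% power: 0.80 points (SD 0.94), 1.19 points (SD 1.40).
- Expected 95% CI half-width: 2.00 × 0.243 = 0.49 points (SD 0.94).

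**4. Judging the hours by their separate comparisons with C.** Simulated trials with A and B identical (4.17 ± 0.94), C at 4.86 ± 1.40, 30 per arm and unadjusted Welch tests: exactly one of A and B differs from C at P < .05 in about 25% of trials. The direct A–B t test is falsely significant in about 5%.

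**The case against.** Several objections carry weight.

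- **Sizing on one of two aims is legitimate.** Effectiveness comes first in 2.1, and group C is there to answer it. This stands: the input suits that aim. It does not support a promise on the other one.
- **The detectability sentence may be only a headcount.** It follows the moxibustion/control figures directly, and the 30 per group after it includes healthy controls. That reading is possible; the text does not settle it, and naming the contrast would.
- **Section 2.13 already provides a direct pairwise test.** It does, and nothing in the plan says an hour will be chosen by comparing each arm's result against C. The 25% figure, from unadjusted tests, shows why that route should be closed; it does not describe a planned analysis.
- **Interpretation rules and interval reporting may sit in an unseen analysis plan.** Fair; their absence is not the point here. The point is what the article affirmatively promises.

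A reader might also infer three stronger things that the documents do not support:

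1. *That the trial will very probably fail to separate A from B.* This depends on the true A–B difference, which is not given. If one hour had no effect at all, the difference could be the full 0.69 and power 74% to 80% with SD 0.94. The pilot's figures cannot be seen.
2. *That sizing on moxibustion versus control could serve A versus B only if the hour mattered more than moxibustion itself.* That follows partly from 26 being too small for its own contrast. With 64 per group and SD 0.94, the A–B difference detectable with 90% power is 0.54, below 0.69.
3. *That the figures with SD 1.40 are equally likely.* That SD belongs to the control arm.

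**Conclusion.** The concern holds in a limited form. The plan gives no A–B difference, and the property stated in 2.12 does not extend to the timing aim. At the planned numbers, power for A versus B is below the stated 90% even when the hours differ by the whole assumed moxibustion effect, and falls to 26–29% at half that effect. The plan can estimate the A–B difference to within about half a DAS28 point either way; it has no stated basis for undertaking to say which hour is better.

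This rests on a two-sided 5% t test, on reading the 90% as power, on SD 0.94 in both moxibustion arms, and on assumed A–B differences. The figures concern DAS28 and say nothing about power on SF-MPQ, for which the article states no sizing basis for this contrast. How far short the trial falls on timing is therefore uncertain; that it was not sized for timing is clear from the text.

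**What to change.** - **Section 2.12.** Limit the detectability sentence to moxibustion versus waiting list. Restate the power there: about 53% at 26 and 60% at 30 per group, two-sided, on the plan's own DAS28 figures. Merely attaching the existing 26 and 90% to that contrast would preserve a wrong figure. Add that the trial was not sized for A versus B, and that at 30 per group about 0.8 DAS28 points is detectable with 90% power if the SD is 0.94 (about 1.2 if it is 1.40). Say that DAS28 is secondary and that SF-MPQ was not used for the sizing.
- **Section 2.13.** State that the timing question is answered only by the direct A minus B difference with its 95% CI (expected half-width about 0.5 DAS28 points at 30 per group, SD 0.94); that a non-significant A–B test is not evidence that the hours are equal; and that no hour is called better because one arm differs from C and the other does not.
- **Section 2.1 and the closing paragraph of section 3.** Replace the promises to determine or point out the better time with an aim to estimate the difference between the two times.

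The cost is wording in four places and a more modest claim on timing. No extra patients, visits or measurements are needed.

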#### 2.11.1. Primary outcome.

##### 2.11.1.1. Short-Form McGill Pain Questionnaire (SF-MPQ).

The SF-MPQ is a multidimensional measure of perceived pain in adults with chronic pain, including pain due to rheumatic diseases. It includes 3 items: the Pain Rating Index, Present Pain Intensity, and Visual Analog Scale (VAS) for average pain. The Pain Rating Index is comprised of 15 words (11 sensory and 4 affective), and each selected word is scored from 0 (none) to 3 (severe). The total Pain Rating Index score is obtained by summing the item scores (range 0–45). Scores on the Present Pain Intensity range from 0 to 5 and on the VAS from 0 to 10. A higher score on the SF-MPQ indicates worse pain.

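### Section 2.12's own DAS28 inputs need 64 patients per group, not 26, for 90% power; 26 gives about 53%, and DAS28 is a secondary outcome

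*Protocol article*

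**What the plan says.** Section 2.12 sizes the trial on DAS28 results from an earlier moxibustion study: 4.17 with SD 0.94 under moxibustion and 4.86 with SD 1.40 under control. The error rates are given in one sentence: "The confidence of the trial sample size was 90% and the significance level was 0.05". The result follows: "Results showed that clinically significant differences would be detected using a minimum sample size of 26 individuals in each group". The recruitment figure is then set: "The maximum permissible withdrawal rate is 15% and 120 participants (30 per group) will be recruited". The 120 include 30 healthy people, so 90 patients are randomised 1:1:1 to morning moxibustion (A), late-afternoon moxibustion (B) and waiting list (C).

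The only measure under the primary outcome heading (2.11.1) is the pain questionnaire, introduced with "The SF-MPQ is a multidimensional measure of perceived pain in adults with chronic pain". DAS28 is item 2.11.2.5, among the secondary outcomes. Section 2.1 sets out to assess whether moxibustion works, "as well as to determine which time is more optimal in clinical practice". Section 2.13 plans one-way ANOVA with multiple comparisons, and t tests for pairs.

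**The concern.** Inputs and result are printed side by side and do not agree. This is therefore not a detail left to a fuller document: no other document can make these inputs yield 26.

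The statement also concerns a different outcome from the primary one, and a different contrast from the comparison of treatment times. A reader of section 2.12 would believe that the trial is very likely to detect the effect it was planned on. On the stated inputs, tested two-sided, the chance is little better than even, and the section says nothing that bears directly on SF-MPQ or on A against B.

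**Working it through.** **Inputs (section 2.12).** Means 4.17 and 4.86, difference 0.69. SDs 0.94 and 1.40. Significance level 0.05. 90%, taken as power because the significance level is given separately in the same sentence. Sidedness is not stated, so both are shown.

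**Common quantities.**
- Sum of variances: 0.94² + 1.40² = 0.8836 + 1.9600 = 2.8436.
- Root-mean-square SD: √(2.8436/2) = 1.192.
- Standardised difference: 0.69/1.192 = 0.579.

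**Attempt to reproduce 26.** Normal approximation, two-sided:

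n per group = (1.960 + 1.282)² × 2.8436/0.69² = 10.51 × 2.8436/0.4761 = 62.8, so 63. The t test, with equal variances or Welch, gives 64.

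Other readings, by noncentral t or noncentral F:

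| Reading | n per group | Power at 26 |
|---|---|---|
| Two-sided 0.05, 90% | 64 | 53% |
| One-sided 0.05, 90% | 52 | 66% |
| Two-sided 0.05, 80% | 48 | 53% |
| One-sided 0.05, 80% | 38 | 66% |
| Two-sided 0.05, 90%, smaller SD (0.94) only | 40 | 74% |
| Three-group ANOVA (4.17, 4.17, 4.86), SD 1.192, 90% | 58 | 55% |

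A Bonferroni correction for two or three comparisons raises the two-sided 90% figure to 75 or 81 (normal approximation).

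Settings that land within two of 26 all depart from the document. They need a one-sided level of 0.10, or power of 70%, or a four-group ANOVA that uses only the SD of 0.94 and gives the healthy group the arthritis control mean. For 26 per group to give 90% power two-sided (normal approximation), the common SD would have to be about 0.77, below both quoted SDs, or the difference about 1.07.

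**Power delivered.**
- At 26 per group: SE = √(2.8436/26) = 0.331; 0.69/0.331 = 2.09. Noncentral t power is 53% two-sided and 66% one-sided.
- At 30 per group: 60% two-sided and 72% one-sided.

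**Detectable pairwise difference with 26 per group (two-sided 0.05, t test).** 0.79 SD at 80% power and 0.92 SD at 90%. SD units apply to any continuous outcome, including SF-MPQ, for which no SD is given. For A against B in DAS28 points, both groups receive moxibustion, so the matching SD is 0.94: about 0.74 points at 80% and 0.86 at 90%.

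**Loss allowance.** 30 × 0.85 = 25.5, just under the stated minimum of 26; 26/0.85 = 30.6, so 31.

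**The case against.** **The text never says power, nor two-sided.** True. But if the 90% is not power, the section states no power at all, and 26 still falls short of 80% with these inputs. One-sided testing softens the shortfall to 66% at 26 and still needs 52 per group.

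**Baseline adjustment could reduce the number.** It could, but reaching 26 takes a baseline correlation of about 0.77. The section states no correlation, and section 2.13 names ANOVA and t tests.

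**The article is condensed, so missing power statements are not errors.** This stands in part. The absence of separate calculations for SF-MPQ and for A against B would not be a finding alone. The mismatch is one, because the article names the primary outcome, names the sizing outcome, and they differ.

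**The comparison of treatment times is less weak than it may look.** This stands. A reader might infer that A against B can only detect a difference larger than the whole assumed moxibustion effect. That comes from applying the SD of 1.192, which mixes in the control group's 1.40: 0.917 × 1.192 = 1.09 points, or 1.6 times 0.69. With the moxibustion SD of 0.94, power for a 0.69-point difference between A and B is 74% at 26 per group and 80% at 30. At 30 the difference detectable with 80% power is 0.736 × 0.94 = 0.69, equal to the assumed effect.

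**The loss allowance is trivial.** Largely so. 26 × 1.15 = 29.9 is a common shortcut, the 15% is a maximum, and section 2.13 plans intention-to-treat with multiple imputation, which keeps withdrawn patients in the analysis though it does not fully restore the lost information.

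**Conclusion.** The claim of 26 per group does not follow from the inputs printed beside it. At a two-sided level of 0.05 the requirement for 90% power is 64 per group, about two and a half times the stated figure (64/26 = 2.5). Delivered power is about 53% at 26 and 60% at 30 per group. One-sided, the figures are 52 per group, 66% and 72%. This assumes that 90% means power, that the quoted means and SDs are used as printed, and that the analysis is unadjusted, as section 2.13 describes. The section calls the DAS28 values mean changes, although the control value is the larger; how they are labelled does not alter the arithmetic.

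Separately, the calculation concerns a secondary outcome and the moxibustion-against-control contrast, not SF-MPQ or the comparison of times.

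Two stronger readings are not supported. The design is not generally blind to an A-against-B difference as large as the assumed moxibustion effect, as the 0.94 figures show. And nothing in the article says that a non-significant A-against-B result will be taken as equal effect. The loss allowance is a minor slip.

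**What to change.** Keep the recruitment target and restate section 2.12:

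1. Replace the claim of 26 per group at 90% with the power delivered for the quoted DAS28 difference: about 53% at 26 and 60% at 30 evaluable per group, two-sided, with 64 per group needed for 90%. State the sidedness, and call the 90% power.
2. Say that the calculation is for a secondary outcome and for moxibustion against control.
3. Add the pairwise detectable difference that applies to SF-MPQ and to A against B: 0.79 SD at 80% and 0.92 SD at 90% power, with 26 per group. If A against B is put in DAS28 points, use the moxibustion SD of 0.94 (about 0.74 and 0.86 points).
4. Minor: align the loss allowance, since 30 per group with 15% loss leaves 25.5.

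The cost is the rewording of one section and a less favourable power statement. No extra patients are needed. The rewording discloses the shortfall; it does not remove it. Sizing the trial on SF-MPQ would need an SD and a target difference for that score, neither of which the article gives.
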